### Analyses

The analyses will be performed according to the íntention to treat' principle. Therefore, all missing values were imputed. In order to replace the missing values by plausible estimates, we will use the regression imputation procedure as implemented in Stata version 9.1 [31].

We will calculate effect sizes for the immediate improvement of the experimental and the control group on the primary and secondary outcomes by dividing the absolute difference between the post-treatment average score and the pretreatment average score by the pretreatment standard deviation. To establish the maintenance of improvement of both groups, effects sizes will be calculated by dividing the absolute difference between the follow-up average score and the post-treatment average score by the pretreatment standard deviation. For between-group effect sizes, the effect size of the experimental group will be subtracted from the effect size of the control group. Effect sizes of 0.56–1.2 can be assumed to be large, while effect sizes of 0.33–0.55 are moderate, and effect sizes of 0–0.32 are small [32].

In the cost-effectiveness analyses, we will calculate the pre-post changes in costs and identify which respondents show a moderate to large improvement in depressive symptoms in both conditions. These respondents changed reliably, and could thus be considered a 'success'. Then we calculated the incremental cost-effectiveness ratio (ICER) across the experimental and control condition, which represents the incremental costs (or savings) per 'success' (i.e. moderate to large improvement in depressive symptoms) in the experimental condition relative to the control condition. Uncertainty will be assessed by means of non-parametric bootstrapping (2,500 times) of the data of the individual respondents.

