### Sample size

In order to demonstrate a standardized effect size of 0.35 (a medium-sized effect [22]) a minimum of eighty participants in each condition is required at the time of the follow-up measurement (t2), based on a statistical power (1-beta) of 0.80, a one-sided test, and a conventional alpha of 0.05 (power calculation in Stata 7.0). Anticipating a drop-out of 20% between t0 and t2, slightly over one hundred participants per condition were included at t0, the baseline measurement.

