### Quantitative study

#### Data collection

##### Overview

Table 1 provides an overview of the economic and effect measurements. As a part of the intake and selection interview, we administer the Center for Epidemiological Studies Depression Scale (CES-D), in order to screen the participants. The outcome is considered the CES-D baseline score for those included; the course starts shortly thereafter. Data at t0 (baseline), t1 (effect; 3 months after t0), and t2 (retention; 6 months after t1) are collected by means of a questionnaire. Demographics and additional personal characteristics are recorded at t0 only, and evaluation questions about the participant's experience with the intervention are asked only at t1. Except for that, the three questionnaires are identical.

**Table 1 T1:** Measurement overview per time (intake, t0, t1, and t2) and research section (clinical, economic and qualitative study)

Variables per research section	Instrument	Intake	T0	T1	T2
Screening and selection					
Examine for depression if CES-D ≥ 16	MINI	×			
Clinical effect evaluation					

*Primary outcome*					
Depressive symptoms	CES-D	×		×	×
					
*Secondary outcomes*					
Anxiety	HADS-D		×	×	×
Locus of control; mastery	Pearlin Mastery Scale (5 items)		×	×	×
Satisfaction with life	MANSA (12 items)		×	×	×
					
*Reminiscence functions*	RFS (4/8 subscales)				
Boredom reduction			×	×	×
Bitterness revival			×	×	×
Identity			×	×	×
Problem solving			×	×	×
					
Economic evaluation					

Cost associated with the receipt of care	TIC-P		×	×	×
Quality of life	EQ 5-D		×	×	×
					
Qualitative study					

Interviews with participants			×			
Observation			×			

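### Regression imputation of all missing values, with no pooling and no named predictors, either understates standard errors or dilutes the effect, depending on whether arm is a predictor

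*Protocol article*

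**What the plan says.** The Analyses section adopts intention to treat and draws a consequence from it: "Therefore, all missing values were imputed". The stated aim is "In order to replace the missing values by plausible estimates", and the stated tool is: "we will use the regression imputation procedure as implemented in Stata version 9.1". Nothing is said about several completed data sets, pooling, residual draws, a variance correction or the predictors used.

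The amount of missing data to expect is in the Sample size section: "Anticipating a drop-out of 20% between t0 and t2, slightly over one hundred participants per condition were included at t0". The same section is the only place that gives a significance level: "based on a statistical power (1-beta) of 0.80, a one-sided test, and a conventional alpha of 0.05".

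The Analyses section then defines standardised pre-post effect sizes and their between-group difference. It calls 0.33–0.55 moderate and 0–0.32 small. For the economic evaluation it defines an ICER per treatment success, with 2,500 non-parametric bootstrap replicates.

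**The concern.** A single regression estimate is not an observation. If it is analysed as one, the analysis counts about 100 people per arm as measured at t2 when about 80 were. If the estimate is also the bare prediction, the filled-in scores have no residual scatter, and the outcome looks less variable than it is. Both push the reported standard error down.

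The step from intention to treat to filling in every value does not follow. Multiple imputation, or a likelihood model on the observed scores, also keeps every randomised participant in the analysis and carries the uncertainty about the missing scores.

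The choice of predictors also matters. A regression that ignores treatment arm pulls the missing scores in both arms towards a common prediction, and so shrinks the difference the trial is meant to estimate. The stated method can therefore fail in two different ways, and the article does not say which applies.

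**Working it through.** **Inputs from the article.** Drop-out is 20% by t2, with slightly over 100 per condition at t0 and 80 needed at t2. The test is one-sided at 0.05 and the target effect is 0.35 SD (Sample size). Imputation covers all missing values (Analyses). The drop-out arithmetic reproduces: 80 / (1 − 0.20) = 100. The article gives no figure for the test's error rate after imputation. Whether 80 follows from the stated power inputs is a separate question that does not bear on this one.

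**Assumptions, not in the article.** Missingness is completely at random. The baseline–outcome correlation is 0.3, 0.5 or 0.7. The imputation model uses baseline, with or without arm.

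**Formula, arm included.** Take deterministic imputation from arm and baseline, followed by ANCOVA on the same two variables, with missing share f. The imputed points lie on the fitted surface, so the estimate equals the complete-case estimate. The residual sum of squares is unchanged but is divided by about n instead of (1 − f)n, so the residual variance is multiplied by (1 − f). The information also appears larger, which is a second factor (1 − f). Hence reported SE / true SE ≈ 1 − f, and the one-sided error is 1 − Φ(1.645 × (1 − f)).

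- f = 0.20: 1 − Φ(1.316) = 9.4%.
- f = 0.10 (assumed): 1 − Φ(1.4805) = 6.9%.

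**Simulation, arm included** (100 per arm, 20% missing, no true effect, 6,000 trials per cell; ranges are over the three correlations):

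| Analysis of completed data | Bare prediction: error | Reported / true SE | One random draw: error | Reported / true SE |
|---|---|---|---|---|
| Change score | 8.2–8.8% | 0.83–0.86 | 7.4–8.4% | 0.85–0.87 |
| t2 score | 7.8–8.9% | 0.80–0.88 | 7.3–8.5% | 0.84–0.90 |
| ANCOVA (assumed) | 9.0–10.0% | 0.78–0.80 | 8.4–9.0% | 0.83 |

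At 10% missing the corresponding errors are 5.9–7.2%.

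**Simulation, arm left out.** The error rate is 4.6–5.5% in every cell, so there is no inflation. The effect is diluted by the missing share instead: 0.35 × (1 − 0.20) = 0.28, and the simulated mean is 0.277. Under ANCOVA with correlation 0.5, the rejection rate at a true 0.35 is 0.80, the same as for complete cases. The damage is therefore to the estimate and its interval, not to power: 0.28 lies in the article's small band, while 0.35 lies in its moderate band.

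**Check of the remedy** (ANCOVA, correlation 0.5, 20% missing, 3,000 trials under no effect):

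| Method | Error | Mean reported SE | Empirical SD |
|---|---|---|---|
| Multiple imputation with arm, 20 imputations, Rubin's rules | 4.9% | 0.138 | 0.135 |
| Complete cases | 5.0% | 0.137 | 0.134 |
| Single imputation with arm, bare prediction | 9.8% | 0.110 | 0.134 |

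At a true 0.35, multiple imputation recovers 0.347.

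**ICER denominator, if imputation is done once before resampling** (4,000 trials per cell; success assumed to be an improvement of at least 0.5 SD; mean control improvement assumed 0.5 SD; correlation 0.4–0.6). The SE used is the large-sample value that resampling the completed data would give.

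- Arm included: the SE of the difference in success proportions is 0.78–0.84 of its true value under no effect. At a true 0.35 the difference itself is 0.144–0.180, against a true 0.125–0.152.
- Arm left out: the spread is about right for the estimator, but the difference is 0.101–0.120, about 20% too small.

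Costs were not modelled.

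**The case against.** The strongest reply is that this is a condensed article. Predictors, residual draws and the number of imputations are details usually left to a full plan, and what the named software procedure does rests on a cited source that is not shown. That stands as far as it goes: single imputation is inferred from the wording and from the absence of pooling, and deterministic prediction is not stated. But the article does name a method, and read as written it is not multiple imputation. If multiple imputation was meant, the sentence needs to say so.

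A reader might infer that the trial will run at a 7–10% false-positive rate for every outcome. The article does not support that, for four reasons:

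- The inflation needs arm as an imputation predictor. Without it, the error is near 5% and the fault is dilution, which works against the course.
- The 20% loss is for t2. No loss is given for t1; at an assumed 10% the inflation is only about 6–7%.
- The top of the range comes from an ANCOVA that appears nowhere in the article. The change-based effect sizes it does describe point to about 8%.
- The one-sided 5% test appears only under Sample size. The Analyses section gives no p-value or interval procedure for the clinical outcomes.

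Lost scatter also does not distort the scale of the primary effect size. That is the pretreatment SD, and the baseline CES-D is the intake score, so those included on that score have it.

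For the economic analysis, the article does not say whether imputation comes before or within resampling, so understated ICER uncertainty is conditional too.

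**Conclusion.** The concern holds in a conditional form. Read as written, the plan is single regression imputation of all missing values, with no predictors named, and it goes wrong on either reading. With arm as a predictor and the article's own 20% loss at t2, standard errors are roughly 10–20% too small and a one-sided 5% test runs at about 7–10%. With arm left out, test size is about right, but a true 0.35 is estimated as about 0.28. The article does not settle which of these applies, so no single direction of error can be claimed.

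If imputation is done once before the 2,500 bootstraps, the ICER inherits the fault: understated uncertainty with arm included, a diluted success difference without it. The figures rest on missingness completely at random, assumed correlations and 100 per arm. The existence of the two failure modes does not depend on the exact correlation.

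**What to change.** Replace the regression imputation sentence with one of two methods. Either use multiple imputation, with arm, intake CES-D and the t1 and t2 outcomes in the model, combined by Rubin's rules; or use a likelihood mixed model on all observed CES-D scores. Both respect intention to treat. For the economic analysis, state that imputation is repeated within each bootstrap sample. The number of imputations and the inclusion of institute are optional choices.

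This needs no new data and no design change. The cost is slightly more analysis work and somewhat wider intervals than single imputation would report. It should be settled before the outcome data are analysed, because the choice of predictors decides which way the result moves.

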##### Primary outcome

1. Reduction of depressive symptoms measured using the Center for Epidemiological Studies Depression Scale (CES-D).

The Center for Epidemiologic Studies Depression scale (CES-D) is a 20-item self-report scale developed to measure depressive symptoms in the community [19]. Subjects were asked to indicate how often they experienced each symptom during the previous week. Response categories, ranging form 0 to 3, were 'rarely or never', 'some of the time', 'occasionally', or 'mostly or always'. Summation results in the CES-D score, ranging from 0 to 60. A score of 16 or higher is considered indicative for clinically relevant depressive syndromes. The psychometric properties of the scale are found to be good in older populations [20].

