##### Secondary outcome

2. Reduction of anxiety symptoms measured using the Hospital Anxiety and Depression Scale (HADS)

The HADS is a 14-item, self-reporting screening scale comprising two 7-item Likert scales, measuring depression and anxiety, respectively. We use the anxiety scale (HADS-A) [24]. Respondents are asked to indicate whether they experienced feelings of restlessness, tenseness, or panic during the past four weeks. Items range from 0 (rarely or never) to 3 (always or most of the time). The total score ranges from 0 to 21.

3. An increase of satisfaction with life measured using the Manchester Short Assessment of Quality of Life (MANSA).

The Manchester Short Assessment of Quality of Life (MANSA) comprises 16 items: 4 objective questions and 12 subjective questions [25]. We use the 12 subjective items, assessing satisfaction with life as a whole, employment or retirement, financial situation, friendships, leisure, accommodation, personal safety, people that the individual lives with (or living alone), sex life, relationship with family, physical health, and mental health. Each item is rated on a seven-point scale ranging from 1 (couldn't be worse) to 7 (couldn't be better). Summary scores range from 12 to 84; the higher the score the better the quality of life.

4. An increase in perceived control over one's life, measured using the Pearlin and Schooler's Mastery Scale.

The Pearlin and Schooler's Mastery Scale consists of seven items that are intended to assess beliefs of perceived control over one's life in general or beliefs regarding one's ability to control an event [26]. We use the abbreviated version of five items, phrased in a negative way. Possible responses are given on a 5-point scale ranging from 1 (strongly disagree) to 5 (strongly agree). Summary scores range from 5 to 25. Higher scores on the scale indicate lower levels of perceived control.

5. Change or transformation into more positive reminiscence styles measured using the Reminiscence Function Scale (RFS).

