Obviously, the research has limitations too. Most of them are related to nonspecific therapeutic benefits that are usually not controlled for in the design of randomized controlled trials, and are inherent in mental health studies of a pragmatic or naturalistic kind. Instead of being put on a waiting list or receiving care-as-usual, for ethical reasons our control group participants are invited to view an informative movie with relevant contents, representing the control condition. In this way, the intervention of which the effectiveness is indicated but not proven yet (Looking for Meaning) is compared with a minimal intervention (movie) of which the effectiveness is unknown. Although a 20-minute movie cannot be expected to rival the impact of a 12-session course, we cannot be sure. Any effectiveness of the movie will lead to an underestimation of the incremental effect size, i.e. the difference between the improvement in the experimental and the control condition. On the other hand, although we encourage therapists to present both interventions with the same enthusiasm, the novelty of the reminiscence course may cause more enthusiasm among the therapists compared to regular courses, leading to an overestimation of the incremental effect size.

The significance of depression for public health especially in older people, underscores the need for preventive interventions. In this study, we investigate the cost(effectiveness) of the indicated prevention course 'Looking for Meaning', which is a well-structured type of life review. Positive results of this study will make an evidence-based intervention to improve public health among older people available.

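### The effect-size rule has no sign convention, so no single reading of it gives the right sign for every outcome it covers

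*Protocol article*

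**What the plan says.** The Analyses section of the protocol article gives three steps for the primary and secondary outcomes together.

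- Immediate improvement, per arm: "dividing the absolute difference between the post-treatment average score and the pretreatment average score by the pretreatment standard deviation".
- Maintenance of improvement, per arm: "dividing the absolute difference between the follow-up average score and the post-treatment average score by the pretreatment standard deviation".
- Between arms: "For between-group effect sizes, the effect size of the experimental group will be subtracted from the effect size of the control group".

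The same paragraph then classifies the results: "effect sizes of 0.33–0.55 are moderate, and effect sizes of 0–0.32 are small", with 0.56 to 1.2 called large. No band exists below 0.

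The outcomes do not all run the same way. For the CES-D (Primary outcome): "A score of 16 or higher is considered indicative for clinically relevant depressive syndromes". HADS-A items rise with the frequency of anxious feelings. For mastery (Secondary outcome): "Higher scores on the scale indicate lower levels of perceived control". For the MANSA the direction is the opposite: "the higher the score the better the quality of life". On the EQ-5D (Economic evaluation), also used as a clinical outcome, 1 is the best health state.

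The Discussion describes the incremental effect size as "the difference between the improvement in the experimental and the control condition".

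**The concern.** A quantity called improvement has to tell better from worse. The rule does not say whether *absolute* means the modulus (sign removed) or the raw, unstandardised difference (sign kept), and it does not orient the scales.

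Under the modulus, deterioration and improvement of equal size give the same number, and control minus experimental makes the hoped-for result negative. With signs kept, one subtraction order cannot suit scales that run in opposite directions.

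At stake are the reported between-group effect sizes and their small, moderate or large labels. These are the stated summary of how much the course helps on each outcome, both after treatment and at follow-up.

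**Working it through.** The article gives no worked effect size and no outcome means or SDs, so there is no figure to reproduce. The check evaluates the rule on assumed means.

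**Inputs**

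- From Analyses: the two within-arm formulas, the subtraction order and the bands.
- From the outcome sections: CES-D, HADS-A and mastery are higher = worse; MANSA and EQ-5D are higher = better.
- Assumed: a pretreatment SD of 8 in both arms, and baseline means of 20 (CES-D) and 50 (MANSA). Changing a common SD rescales every result and alters no sign.

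**Formulas**, with dE and dC the later mean minus the earlier mean in the experimental and control arms

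- Modulus reading: abs(dC)/SD − abs(dE)/SD
- Signed reading: (dC − dE)/SD
- Benefit of the course: (dC − dE)/SD where higher is worse; (dE − dC)/SD where higher is better

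**Case 1 in full.** dE = 16 − 20 = −4 and dC = 18.8 − 20 = −1.2. Modulus: 1.2/8 − 4/8 = 0.15 − 0.50 = −0.35. Signed: (−1.2 + 4)/8 = 2.8/8 = +0.35. Benefit: +0.35.

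| Case | Experimental | Control | Modulus reading | Signed reading | Benefit |
|---|---|---|---|---|---|
| 1. CES-D, both improve | 20 to 16 | 20 to 18.8 | −0.35 | +0.35 | +0.35 |
| 2. CES-D, control worsens | 20 to 18 | 20 to 21.6 | −0.05 | +0.45 | +0.45 |
| 3. CES-D, equal and opposite | 20 to 18.6 | 20 to 21.4 | 0.00 | +0.35 | +0.35 |
| 4. CES-D, experimental worsens | 20 to 24 | 20 to 18.8 | −0.35 | −0.65 | −0.65 |
| 5. MANSA, both improve | 50 to 54 | 50 to 51.2 | −0.35 | −0.35 | +0.35 |

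**Modulus reading.** In case 1 the size is right and the sign reversed, and the value has no band. In cases 2 to 4, where the arms move in opposite directions, the size is wrong. Cases 1 and 4 both give −0.35, although one is a benefit of 0.35 and the other a harm of 0.65. With control unchanged, an experimental change of 0.35 SD gives 0 − 0.35 = −0.35 whether it is better or worse.

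**Signed reading.** The between-group value is correct on the CES-D in all four cases, and by the same algebra on HADS-A and mastery. On the MANSA (case 5) it is reversed: (1.2 − 4)/8 = −0.35 for a benefit of +0.35. Where higher is better, dC − dE is exactly the negative of the benefit, so EQ-5D is reversed too. Taking pre minus post only moves the error. MANSA becomes (−1.2 + 4)/8 = +0.35, and CES-D in case 1 becomes (1.2 − 4)/8 = −0.35.

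**Maintenance.** Suppose the experimental CES-D mean relapses from 16 to 19. The within-arm value is 3/8 = 0.375, which the bands call moderate, under the name of maintained improvement. An arm that keeps its gain fully (16 to 16) scores 0, the bottom of the small band.

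**The case against.** The best defence is that *absolute difference* means the raw difference before standardisation. The order of terms (post before pre, then experimental subtracted from control) makes benefit positive on the CES-D. That agrees with bands starting at 0 and with the Discussion. This stands for the between-group value on the primary outcome, HADS-A and mastery. It does not stand for MANSA and EQ-5D, to which the same rule applies.

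A reader might go further and infer three things that the article does not support.

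- *That the primary result will be reported with the wrong sign.* This follows only on the modulus reading. Even then, if both arms improve, the magnitude is right.
- *That a wrong size is to be expected because life review can be burdensome.* The Background says this of some older adults, that is, of individuals. The rule works on arm means, and nothing in the article predicts a mean worsening from baseline in either arm. Worsening between post-treatment and follow-up is more plausible, and there the maintenance formula would hide it.
- *That the trial's inference rests on this rule.* Research question 1 asks about a significant reduction, and Sample size refers to a one-sided test, so a separate between-group test is intended. Its form may be set out in a fuller plan, and its absence from the article is no fault.

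It is also fair that the intended direction of each clinical outcome is mostly clear from its description, and that anyone computing these values from the means would see which way the means moved.

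**Conclusion.** The point holds as a defect in a stated reporting rule, and it should be fixed. No single reading gives the right sign for every outcome covered. The modulus reading reverses the sign when both arms improve, gives the wrong size when their means move in opposite directions (0.00 for a benefit of 0.35 in case 3), and scores relapse as maintained improvement. The signed reading is right between arms for CES-D, HADS-A and mastery, and reversed for MANSA and EQ-5D.

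The signs follow from the formulas alone. The sizes rest on the assumed means and SD of 8 and are illustrations, not predictions. No hypothesis test, sample size or eligibility rule is shown to depend on this rule, so the point does not threaten the trial's conclusions in themselves.

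**What to change.** In Analyses:

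1. Delete *absolute* from both formulas, the post-treatment one and the maintenance one.
2. Define signed improvement by scale: earlier minus later mean where lower is better (CES-D, HADS-A, mastery), later minus earlier where higher is better (MANSA, EQ-5D). State the favourable direction for each reminiscence subscale as well.
3. Define the between-group effect as experimental minus control, so that a positive value favours the course, in line with the Discussion.

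In the maintenance formula, a negative value then means loss of the gain. A pooled SD or a confidence interval may be worth having, but neither cures the sign problem and neither is part of this correction. The cost is a few sentences of wording, with no change to data collection, sample size or participant burden.

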1. Does the prevention program Looking for Meaning lead to a significant reduction of depressive symptoms and a significant enhancement of wellbeing, satisfaction with life, and quality of life in elderly people with depressive symptoms, in comparison with a no-treatment control group?

2. Which prognostic factors (demographic, clinical symptoms, mastery), in combination with the intervention, predict lower or higher effects on depressive symptoms, wellbeing, satisfaction with life and quality of life?

3. What is the incremental cost-utility in the treatment group as compared to the control group?

4. Which are the working components of the intervention, leading to reduction of depression and enhancement of wellbeing, mastery and satisfaction with life, according to the participants?

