### Randomization

Participants are randomly assigned to either of the two research conditions by means of a centrally conducted randomization stratified for gender. This means the randomization takes place at the research institute (Netherlands Institute of Mental Health and Addiction), independent of the participating institutions; they receive the outcome of the procedure in the regular mail and are to schedule the participants accordingly.

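### The between-arm effect size is a difference of two standardised changes with no interval or test attached; a baseline- and gender-adjusted model would be more precise at no extra data cost

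*Protocol article*

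**What the plan says.** The first research question in the Background asks whether the course will "lead to a significant reduction of depressive symptoms", judged "in comparison with a no-treatment control group". The Sample size section starts from "In order to demonstrate a standardized effect size of 0.35" with 80% power, a one-sided test and alpha 0.05, and arrives at 80 per condition at follow-up.

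The Analyses section then defines the clinical effect measures in three steps.

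- Immediate improvement in each arm comes from "dividing the absolute difference between the post-treatment average score and the pretreatment average score by the pretreatment standard deviation".
- Maintenance in each arm comes from "dividing the absolute difference between the follow-up average score and the post-treatment average score by the pretreatment standard deviation".
- The arms are compared by one subtraction: "For between-group effect sizes, the effect size of the experimental group will be subtracted from the effect size of the control group".

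The results are graded small (0 to 0.32), moderate (0.33 to 0.55) or large (0.56 to 1.2). The only uncertainty method in the section is "Uncertainty will be assessed by means of non-parametric bootstrapping (2,500 times) of the data of the individual respondents", and it stands in the cost-effectiveness paragraph.

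Two design features do not appear as covariates. The intake CES-D serves as the baseline score for everyone included (Data collection, Overview), and allocation uses "a centrally conducted randomization stratified for gender" (Randomization).

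**The concern.** The article commits to a particular statistic for comparing the arms, and a better one can be had from the same data. Three things follow.

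- **No stated uncertainty.** As written, the clinical between-arm effect size is a point value with a grade. Nothing links it to the one-sided test assumed in the Sample size section.
- **Lost precision.** Subtracting the baseline mean uses baseline with a fixed slope of one. When the pre-post correlation is below one, that is noisier than estimating the slope, and chance baseline imbalance is not removed as well.
- **Analysis does not follow design.** Randomisation was stratified for gender, but gender is not in the stated comparison.

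At stake are the precision of the primary result and the risk that a grade is read as a conclusion.

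**Working it through.** **Inputs from the protocol article.** d = 0.35, one-sided alpha 0.05, power 0.80, 80 per arm at t2, 20% drop-out (all Sample size). Baseline CES-D is collected (Overview, Table 1); gender is the stratum (Randomization).

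**Assumptions.** The pre-post correlation r is not given, so it is varied from 0.3 to 0.8. SDs are taken as equal across arms and times, and the SD used for standardising is treated as known. The change score is measured from baseline. The normal approximation is used.

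**The plan's own figure.** With a plain two-sample comparison, n per arm = 2 × ((1.645 + 0.842)/0.35)² = 100.9, so 101. The stated 80 does not reproduce; at 80 per arm the power is 71.5%. The drop-out step does reproduce: 80/(1 − 0.20) = 100. The 80 would fit a baseline-adjusted analysis with r of about 0.46, or a change score with r of about 0.60, but the article states neither. This is a separate matter and is given only as context.

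**Variances, in units of the baseline variance.**

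- Change score: 2(1 − r)
- Baseline-adjusted (ANCOVA): 1 − r²
- Ratio, adjusted to change: (1 − r²)/(2(1 − r)) = (1 + r)/2, which is below 1 for every r below 1

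**Power at 80 per arm.** Power = Φ(0.35/(s√(2/80)) − 1.645), where s is the square root of the variance above. Example at r = 0.4:

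- Change: s = √1.2 = 1.095, SE = 1.095 × 0.158 = 0.173, 0.35/0.173 − 1.645 = 0.376, power 64.6%.
- Adjusted: s = √0.84 = 0.917, SE = 0.145, 0.35/0.145 − 1.645 = 0.770, power 77.9%.

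| r (assumed) | Variance ratio | Power, change | Power, adjusted | 95% half-width, change | 95% half-width, adjusted |
|---|---|---|---|---|---|
| 0.3 | 0.65 | 58.9% | 75.0% | 0.367 | 0.296 |
| 0.4 | 0.70 | 64.6% | 77.9% | 0.339 | 0.284 |
| 0.5 | 0.75 | 71.5% | 81.9% | 0.310 | 0.268 |
| 0.6 | 0.80 | 79.7% | 86.9% | 0.277 | 0.248 |
| 0.7 | 0.85 | 88.7% | 92.7% | 0.240 | 0.221 |
| 0.8 | 0.90 | 96.8% | 98.0% | 0.196 | 0.186 |

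**What a grade hides.** Take an observed change-score difference of 0.35, graded moderate. At r = 0.5 its 95% interval is 0.35 ± 0.31, or 0.04 to 0.66, which runs from small to large. At r = 0.8 it is 0.35 ± 0.196, or 0.15 to 0.55, which runs from small to moderate.

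**Gender.** The article gives no association between gender and outcome, so no gain from adjusting for it can be computed.

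**The case against.** **The plan has no test, so it cannot answer its first question.** A reader might infer this, but the document does not support it. The Sample size section foresees a one-sided test, and the Analyses section is visibly not complete: it describes no analysis for research question 2, on prognostic factors. A full protocol or analysis plan may name the test. What stands is narrower: the article attaches no test or interval to the between-arm statistic that it does define.

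**Baseline is ignored.** This is not so either. Each arm's pretreatment mean is subtracted, and a difference in mean change between randomised arms is a valid, unbiased contrast. The point is efficiency and residual sensitivity to chance imbalance.

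**The change score leaves the trial short of power.** That cannot be said in general. At r = 0.6 the change score already gives about 80% power, and at r = 0.8 the gap to the adjusted analysis is about one percentage point.

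**Omitting gender is harmless.** Leaving out a stratification factor does not bias the mean difference and tends to be conservative. This stands, so the case for gender rests only on analysing as randomised.

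None of these objections makes the stated statistic as good as the adjusted one. For every r below 1 the adjusted variance is lower, using data already in hand.

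**Conclusion.** The point holds as an improvement to a stated method, not as an error that invalidates the comparison. The article defines the clinical between-arm result as a difference of arm-level standardised changes, without an interval, test or covariate attached to it. Adjusting for baseline CES-D would cut the variance by 10% (r = 0.8) to 35% (r = 0.3). At 80 per arm and d = 0.35 the power gain is about 16 percentage points at r = 0.3, 10 at r = 0.5, 4 at r = 0.7 and 1 at r = 0.8.

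These sizes rest wholly on r, which the article does not give, and on equal SDs. The direction of the gain does not depend on the value of r below 1. The gain from gender adjustment cannot be quantified.

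**What to change.** Derive the between-arm effect from an ANCOVA of CES-D on arm, baseline CES-D and gender, or from a mixed model over t1 and t2 with the same covariates. Then:

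- Report the signed adjusted mean difference with its 95% confidence interval and p value, and say whether the p value is the one-sided one assumed in the Sample size section. The sign matters because the stated arm-level measures are absolute differences.
- Obtain the standardised effect by dividing that difference by one pooled baseline SD, and apply any grading to the estimate together with its interval.
- Keep the arm-level change effect sizes as description.
- Use the same model for each secondary outcome with its own baseline.

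The cost is a change of analysis wording, best made before outcome data are compared by arm. Baseline scores are already collected and gender is known from randomisation, so no new data or participants are needed. If a fuller analysis plan already specifies such a model, the article's wording only needs to be aligned with it.
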